## Abstract

**Background:**

Venous ulcers have a prevalence of 1% in Western countries, with a tendency to become chronic and recur frequently. The lengthy periods of healing required for the treatment of these lesions result in increased costs. It is possible that patient education may enhance patients’ understanding of their health condition, which could potentially lead to a reduction in recurrence rates. Nevertheless, it is uncertain whether this constitutes the optimal educational strategy.

**Objective:**

The objective of this study is to assess the superiority of an educational intervention delivered via video compared to an informative brochure in outpatient nursing clinics, focusing on patients’ knowledge of venous leg ulcers and their self-care skills.

**Methods:**

A total of 144 patients with venous leg ulcers who attend the outpatient nursing clinics will be recruited to participate in this randomized controlled trial. Individuals with cognitive impairment, an ankle-brachial index of less than 0.90, arterial insufficiency, and arterial ulcers or ulcers of mixed origin will be excluded from the study. The intervention comprises 4 short educational videos specifically created for this study, in which patients will be provided with information on disease knowledge, medication management, compression therapy, and the importance of adequate nutrition and physical activity. The control group will be provided with the standard education offered at the outpatient clinics participating in the study, which will be disseminated through an information leaflet. Patient assessments will be performed with standardized, validated tools at baseline; at 1, 3, and 6 months postenrollment; and at 12 months via telephone follow-up. The primary outcomes are the patient’s level of knowledge and their ability to self-care. The secondary outcomes are the patient’s level of well-being, the success rate of the treatment, and the recurrence rates. A preliminary feasibility study was conducted to methodologically refine the protocol.

**Results:**

A feasibility study was conducted to refine study procedures and data collection tools, confirming the acceptability of the questionnaires and the feasibility of digital data collection. The randomized controlled trial was funded in June 2025. It is currently pending ethics approval, and it is expected to start recruitment in spring 2026. Results from the main trial are expected to be available by the end of 2027.

**Conclusions:**

A video-based educational intervention may prove to be an effective, readily accessible, and replicable method of patient education. The findings of this study will inform the most effective method of patient education for this population, ensuring the delivery of high-quality care and enhancing the quality of services.

## Introduction

Venous leg ulcers (VLUs) are defined as skin lesions on the lower leg or foot with a healing time of more than 6 weeks [1]. These dermatological conditions occur in the lower extremities as a consequence of elevated venous pressure, leading to vascular dilation and fluid stagnation in the affected areas. VLUs are a complication of chronic venous insufficiency, which causes damage to the vessel walls and surrounding tissues. They account for 70% of all leg ulcers [1]. In addition to venous insufficiency, several factors, such as age, reduced mobility, and obesity, have been identified as contributing to the development of VLUs [2].

The incidence of VLUs is increasing among adults, particularly among older adults who often have concomitant diseases. It affects 1% of the global population between the ages of 18 and 64 [3]. In the United States and other Western countries, the prevalence of this condition is estimated to be approximately 3% among the older adults [4-6].

In clinical practice, the treatment of VLUs typically involves prolonged healing periods and a high rate of recurrences [7,8]. A review of the literature shows that 22% of individuals who recover from VLUs will experience a recurrence within 3 months, 57% within 1 year, and up to 78% within 3 years. Furthermore, the risk of recurrence is 4.4 times higher in patients with a history of multiple VLUs [1], leading to increased treatment needs and health care costs. The diagnosis, treatment, and cure of VLUs account for up to 2% of the annual health care budget of Western societies [6].

A wound that persists for more than 1 month without following the normal healing process is classified as a chronic wound [3]. This chronicity is associated with a diminished quality of life. Patients frequently report a range of symptoms and experiences, including pain, sleep disturbances, malodor, impaired mobility, altered body image, reduced energy levels, and dissatisfaction with treatment. These symptoms and experiences can lead to a significant decline in perceived quality of life, encompassing physical, psychological, and social domains [1,9,10]. Additionally, VLUs can result in leg weakness, swelling, exudation, and recurrent infections [4].

Given the chronic and prevalent nature of these ulcers, patients or their caregivers frequently take on the responsibility of managing and providing self-care for VLUs. This involves maintaining health, monitoring the condition, and managing any issues that arise. The maintenance phase focuses on the prevention of injuries or recurrences through the reduction of risk factors. Monitoring involves observing signs and symptoms, while management encompasses the patient’s response to any observed signs and symptoms [8]. A significant barrier to effective VLU self-management is the lack of adequate health information [11]. This gap in knowledge limits the ability of patients or their caregivers to maintain health, monitor the condition, and manage the wound effectively. Therefore, it is crucial to ensure that patients are fully informed about their health condition, associated risk factors, potential complications, protective measures, and available treatment options for managing symptoms.

Noninvasive treatments for VLUs include the application of local dressings to the wound and surrounding skin, as well as the use of compression therapy. The literature shows that compression therapy is a more effective method for promoting healing compared to the application of local dressings alone, resulting in a reduction of the wound surface area by 30% [4]. Furthermore, the proper application of compression therapy has been demonstrated to reduce pain, alleviate pressure, and decrease volume overload in the venous system [12], thereby improving venous and lymphatic return [4]. Given the high recurrence rates at 12 months postwound healing, it is crucial to maintain preventive measures, particularly compression therapy, in order to mitigate the risk of recurrence [13,14].

Unfortunately, a significant proportion of patients either do not adhere to or only partially adhere to compression treatment [15]. Nonadherence to recommended compression therapy is associated with a significant increase in the risk of delayed wound healing and recurrence, with estimates ranging from 2 to 20 times higher [5]. Adherence is influenced by a number of factors, including receiving conflicting information [16] or a lack of clear, objective, and easily understandable information [17]. Additionally, adherence is influenced by the individual’s beliefs about the effectiveness of the treatment, their awareness and knowledge of the condition [14], and the level of patient involvement in the management of their VLU [3]. A deeper understanding of their condition empowers patients to engage in effective self-care and avoid risky behaviors [8]. Therefore, it is crucial to promote adherence to continuous compression therapy through patient education [17] to enhance knowledge and prevent recurrence.

However, the consistency of patient education across different health care settings remains variable, and there is a lack of robust scientific evidence regarding the effectiveness of interventions [14,18]. The educational interventions provided to patients with VLUs in outpatient clinics often lack clear and consistent guidelines for delivery, with the approach being dependent on the individual health care provider. In cases of high workload, a standardized tool is not always guaranteed, and education may be completely absent, as reported by the clinicians involved in this care setting.

A method for patient education described in the literature involves face-to-face sessions lasting 20 to 60 minutes, conducted at the patient’s home or in the outpatient clinic, with or without written material [1]. However, given the high prevalence of VLU, it is often not feasible to carry out such lengthy sessions due to staffing limitations. Another effective educational method involves participation in a community of VLU or healed patients, where experienced VLU nurses provide education. However, transportation issues and limited availability make it difficult for all patients to attend these meetings [19].

Another potential strategy for the dissemination of information and the promotion of awareness is the use of manuals, brochures, or small books. These resources can facilitate the dissemination of knowledge and enhance the understanding of the general population, enabling patients and their families to refer back to them multiple times and support decision-making in the management of VLU [20]. A study conducted in Italy at a vulnology clinic for ambulatory patients with VLUs demonstrated that providing an informational brochure can improve patient education, particularly in self-care capacity and disease knowledge [15]. Conversely, a study conducted by Baquerizo Nole et al [21] suggests that illustrative video recordings may be even more effective in enhancing patient knowledge compared to brochure-based education.

Indeed, educational videos are easily accessible, can be displayed in clinic waiting rooms, do not require the ability to read or comprehend written text, and also ensure that patients receive accurate and consistent information, reducing communication errors attributable to the disparate experience of health care providers or potential information distortion. In addition, video-based education could facilitate personalized care by allowing patients to request further information or specific advice from professionals. This enables nurses to prioritize delivering more relevant guidance instead of repeating information the patient may already know. These considerations make them a potentially superior method of education. However, the results of previous studies have not been statistically significant due to the limited number of enrolled patients [21].

On these premises, a project was developed to assess the superiority of an educational intervention delivered via video compared to an informational brochure in outpatient nursing clinics, focusing on patients’ knowledge of VLUs and their self-care skills. The aim of this article is to present the protocol for this clinical trial.

## Methods

### Study Design

#### Study Setting and Design

The study is a randomized, controlled, single-blind trial with 2 parallel groups. The aim is to assess the effectiveness of the experimental intervention in increasing the level of knowledge and self-care skills of patients with VLUs compared to the standard of care provided in outpatient nursing clinics, where education is delivered through an informational brochure. The intervention comprises an educational video on VLU management. Patients are randomized using block randomization in order to prevent imbalance between the intervention and control groups over the course of the 12-month study period.

As a parallel project, a longitudinal prospective substudy will be dedicated to validating the Italian version of the Well-being of Wounds Inventory (WOW-I) questionnaire.

The protocol was developed in accordance with the SPIRIT (Standard Protocol Items: Recommendations for Interventional Trials) 2013 statement [22].

#### Eligibility Criteria and Exclusions

Patients attending the outpatient nursing clinics involved in the study will be enrolled. To be eligible to participate in the study, patients must meet all of the criteria set out in Textbox 1. These include being aged 18 years or older, having a VLU, understanding Italian, being able to read and comprehend the questions, providing consent to participate in the study, and having access to a smart device with internet connectivity or a caregiver able to provide such a device. Individuals with cognitive impairment, an ankle-brachial index of less than 0.90, arterial insufficiency, or ulcers of arterial or mixed origin will be excluded from participation.

Textbox 1.Eligibility criteria.
**Inclusion criteria**
Aged 18 years or olderAffected by venous leg ulcerAble to understand the Italian languageAble to read and understand the questionsAttending the nursing clinics involved in the studyProvided consent to participate in the studyAble to use a smart device with internet access or supported by a caregiver able to use a smart device as a video player
**Exclusion criteria**
Cognitive impairmentAnkle-brachial index less than 0.90 or arterial insufficiencyArterial or mixed-origin ulcers

#### Randomization and Blinding

After obtaining informed consent and confirming eligibility criteria, randomization will be conducted using the REDCap (Research Electronic Data Capture; Vanderbilt University) platform. Patients will be randomly assigned to 1 of 2 parallel groups in a 1:1 ratio, using block randomization to ensure balance between the 2 groups during the follow-up.

The study is single-blind. Two separate teams, blind and unblind staff, will be created and assigned different activities to be performed. Nurses belonging to the blind staff will be responsible for assessing patients and delivering a blinded QR code, thereby preventing them from knowing which intervention is assigned to each participant. The unblind staff will have access to all other information except clinical assessments and will serve as the appointed contact point for patients and their caregivers regarding any study participation–related issues, thus preventing any potential risk of unblinding. Patients’ and caregivers’ questions (related to study participation or clinical care) will be directed only to the unblind staff. Both the blind staff and the patients or caregivers will be informed of this logistic before the study starts and reinforced during the study conduction and follow-up.

#### Experimental Treatment

The experimental educational intervention consists of 4 short, professionally produced videos covering the following topics: VLU knowledge, medication management, compression therapy, and diet and physical activity.

The content of the videos was derived from a thorough literature review and further refined by 2 expert nurses specializing in wound care. The videos were recorded by an experienced videographer in collaboration with a patient volunteer, 2 nursing students, and 2 nurses with expertise in managing VLUs.

In each video, the presenter provides clear and accessible explanations, using language that is easily comprehensible to the general public. When medical terminology is used, a definition is provided. Additionally, key terminology used by the speaker is displayed on the screen, accompanied by realistic images and scenes relevant to the discussed topics, enhancing comprehension through visual representation.

The first video is approximately three and a half minutes long and provides an overview of VLUs, their anatomical location, the associated risk factors, the mechanisms of development, and the diagnostic criteria.

The second video, lasting approximately 5 minutes, provides an in-depth exploration of the importance of treating VLUs, various management and treatment approaches, and potential complications.

The third video, 7 minutes long, explains the concept of compression therapy, its benefits and contraindications, the proper technique for applying elastic stockings, and lifestyle changes, including advice on physical activity to prevent the development of ulcers.

The fourth video, which lasts about 2 minutes, presents a list of foods and nutrients that promote the healing of VLUs and help prevent their recurrence.

The videos were uploaded to a YouTube channel accessible only to individuals possessing the requisite link or QR code. This was done to prevent contamination and ensure the integrity of the study. The platform allows the researcher to determine the number of views, which serves as an indicator of adherence to the experimental treatment. To track the views of each participant, every person in the experimental group will receive the same videos but will view a differently uploaded version.

Consequently, each video link or QR code will be associated with an alphanumeric identification number assigned to a participant, a strategy that will allow researchers to link the questionnaires completed by each participant to the number of views of the individual videos. Participants will be required to retain the link or QR code for viewing the intervention, as it will differ from the links or QR codes of other participants in the study.

#### Video Intervention

A document containing an identification number and QR codes or links will be provided to participants who have been assigned to the intervention group. The identification code, which the patient is required to retain and keep secret, is alphanumeric and random. The code is used by the participant to complete the questionnaires at baseline and during the follow-up periods, with the intention of guaranteeing anonymity. The QR codes and links serve the purpose of enabling the patient to access the 4 experimental educational videos. Patients assigned to this group will be required to access the videos via QR codes or links and view them after completing the baseline questionnaires or within the initial 7-day enrollment period. The educational intervention can be viewed in the outpatient nursing clinic after the visit, in a waiting room, with one’s own smart device or a device provided by the company, or at the participant’s home.

The videos may be viewed on multiple occasions during the study period. The outpatient nurse will issue a reminder to the patient to view the intervention at least once.

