#### Control Treatment

Similarly, the control group will receive a document containing an alphanumeric identification number and a link or QR code. The identification code will be used in the same way as it is used for the intervention group, allowing participants to complete the questionnaires at the baseline and follow-up stages. The QR code will instead direct participants to a printable educational brochure. This brochure represents the standard treatment. It was introduced following a study conducted in 2021 that demonstrated its efficacy in increasing patient compliance, self-care skills, and disease knowledge in patients with VLUs [15]. Since then, it has been routinely used to educate VLU patients in the study settings. The educational content in the brochure covers some of the topics presented in the educational videos but in a short form, such as the nature of venous ulcers, the available treatments and compression therapy, dressing management, potential risks and complications, and beneficial lifestyle changes. The brochure will contain both written text and illustrative images and will be available to participants throughout the duration of the study.

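### The link restriction controls who can open the videos, not who sees or hears them, and waiting-room viewing leaves control patients and blinded nurses open to exposure

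*Protocol article*

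**What the plan says.** All references are to the protocol article.

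- **Experimental Treatment** describes four narrated videos with key terms and images on screen. Access is limited: "The videos were uploaded to a YouTube channel accessible only to individuals possessing the requisite link or QR code". The stated reason follows: "This was done to prevent contamination and ensure the integrity of the study". Each participant has a separately uploaded copy, so views are counted per link holder.
- **Video Intervention** sets where they may be watched: "The educational intervention can be viewed in the outpatient nursing clinic after the visit, in a waiting room". The patient may use a personal or a company device, and may watch at home instead. First viewing is due after the baseline questionnaires or within 7 days, and repeat viewing is allowed.
- **Eligibility Criteria and Exclusions** defines one recruitment source for both arms: "Patients attending the outpatient nursing clinics involved in the study will be enrolled".
- **Randomization and Blinding** allocates by person: "Patients will be randomly assigned to 1 of 2 parallel groups in a 1:1 ratio, using block randomization". Nurses on the blind staff assess patients and hand out a blinded QR code so that they do not learn the allocation.
- **Control Treatment** gives the comparator: "The QR code will instead direct participants to a printable educational brochure". The brochure covers part of the video content, in shorter form.

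**The concern.** The only contamination safeguard described acts on access to the file. It does nothing about a bystander while the video plays, and the article expressly permits playback in a clinic setting that patients of the other arm also attend.

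Three things are at stake.

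1. **The primary contrast.** What separates the arms is the video content beyond the brochure. A control patient who picks up some of it before the 4-week assessment narrows the difference in a superiority trial.
2. **The hierarchy.** Under Sample Size Calculation, VeLUSET is evaluated only if VLUK is significant. Dilution of VLUK alone could therefore cost both coprimary claims.
3. **Blinding.** Visible or audible playback in the clinic may show blinded nurses who is in the video arm. VLUK and VeLUSET are self-completed, so this bears mainly on the nurse-scored PUSH Tool.

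View counts belong to the video-arm link holder, so they would not show exposure of a control patient.

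**Working it through.** **Step 1. Do the passages leave a route?** The link rule answers the question of who can start a video. The viewing rule answers where it may be played. Recruitment from the same clinics and allocation by individual mean that both arms can be in one clinic at the same time. Running time is about 3.5 + 5 + 7 + 2 = 17.5 minutes. Early and repeat viewing are both allowed, so exposure before a control patient's 4-week assessment is possible. The route exists. How often it is used is not stated.

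**Step 2. Which error level do the plan's own figures imply?** Sample Size Calculation gives Z > 2.54 at the interim and nominal P values of .006 and .048. With Lan-DeMets O'Brien-Fleming spending at half the information, the error spent at the interim is 2 × [1 − Φ(z(1−α/2) / √0.5)], where α is the one-sided level.

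- One-sided 5%: 1.960 / 0.7071 = 2.772, error spent .0056, Z = 2.538; final P = .0482. This matches 2.54, .006 and .048.
- Two-sided 5%: Z = 2.963, P = .0031; final P = .0490. This does not match.

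The one-sided basis is therefore used below.

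**Step 3. The plan's sample size.** The 72 per group cannot be reproduced forwards, because no effect size or SD is given. Working backwards with 10% dropout, 64 evaluable per arm gives 64 / 0.9 = 71.1, rounded up to 72. The implied standardised difference at 80% power is 0.44 (one-sided 5%).

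**Step 4. Power if part of the contrast is lost.** Let c be the fraction of the video-versus-brochure difference lost through control-arm exposure. This is an assumption; no value is in the document. In a fixed-sample approximation that ignores the interim look:

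- noncentrality = 1.6449 + 0.8416 = 2.4865
- power = Φ((1 − c) × 2.4865 − 1.6449)
- evaluable per arm to restore 80% = 64 / (1 − c)², rounded up, then divided by 0.9 and rounded up

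| c | Argument of Φ | Power | Randomised per arm for 80% |
|---|---|---|---|
| 0 | 0.8416 | 80.0% | 72 |
| 2% | 0.7919 | 78.6% | 75 |
| 5% | 0.7173 | 76.3% | 79 |
| 10% | 0.5930 | 72.3% | 89 |
| 20% | 0.3443 | 63.5% | 112 |

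On a two-sided 5% basis the powers would be 78.4%, 75.9%, 71.3% and 61.1%, so the choice changes little.

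**Step 5. What c means.** A value of 5% corresponds to 5% of controls gaining the whole video effect (0.05 × 64 = 3.2 patients), or to 20% of controls gaining a quarter of it (0.20 × 0.25 = 0.05).

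**The case against.** The strongest reply is that the two sections do not contradict each other. Personal links still stop controls from opening or finding the videos, wherever the holder watches. Viewing is on one person's device, after the visit, with home as an alternative. Earphones and seating are details that an article may leave to site instructions. All of this is fair, except that the point does not rest on silence: the article itself names the waiting room as a permitted place, and that permission is what needs a condition.

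Opportunity also looks limited. With 72 video patients enrolled over about 6 months (26 weeks), a 4-week window holds about 72 × 4 / 26 = 11 first viewings, spread over several clinics and partly at home. A control would have to be present and take in another person's video. This argues for the low end of the table, and it stands.

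Two further replies carry weight. Bias toward no difference cannot produce a false claim of superiority. And the interim conditional-power step, if it means sample-size re-estimation, might recover some lost power.

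A reader might infer more: that the waiting room is known to be shared with control patients, that the safeguard is defeated, or that the contrast is in fact diluted. The article supports none of these. Sharing is a reasonable inference from common clinics and individual allocation, but it is not stated. The access control still works for what it covers. Dilution is possible but not shown.

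**Conclusion.** The point holds in a limited form. The stated safeguard leaves bystander exposure uncontrolled, and the permitted viewing place makes that exposure possible for control patients before the primary assessment. It may also reveal allocation to blinded nurses.

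The size is unknown. A loss of 2% to 5% of the contrast would cost about 1 to 4 points of power; 10% would cost about 8 and 20% about 16 to 17. The larger values need substantial exposure, for which the article gives no evidence. These figures rest on the stated 80% power, a one-sided 5% level inferred from the boundaries, an assumed c and a fixed-sample approximation. The case for acting rests on how cheap the repair is and on recruitment not having begun, not on a demonstrated loss.

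**What to change.** Amend the Video Intervention section so that in-clinic viewing is with earphones on a personal screen, or in a space away from other trial patients and blinded staff. Keep home viewing and the company devices. The Introduction counts waiting-room display among the advantages of video, and lower viewing in the video arm would itself weaken the intention-to-treat contrast.

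Optionally, record whether control patients saw or heard the videos, for descriptive reporting only. It should not drive an analysis that excludes or stratifies patients, because conditioning on post-randomisation self-report gives up the protection of randomisation. Asking both arms about the other arm's material would add little: the brochure is already routine in these clinics, so video patients may well have met it.

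Cost: a sentence in the protocol and site instructions, inexpensive earphones, and slightly less convenience for patients who want to watch before leaving.
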